### Objectives {7}

The primary objective of the WONDER-01 trial is to evaluate the superiority of immediate DEN over drainage-oriented step-up approach following EUS-guided drainage of WON in terms of time to clinical success. The secondary objectives include assessments of a technical success rate, procedure-related adverse events, and long-term outcomes (detailed in Table 1).

**Table 1 Tab1:** The primary and secondary endpoints of the WONDER-01 trial

Primary endpoint	Secondary endpoints
Time from randomisation to clinical success^a^	Incidence of procedure-related adverse events graded by the AGREE classification [25] as well as the ASGE lexicon guideline [26]
Clinical success is defined as (1) a decrease in a WON size to 3 cm or less and (2) an improvement of at least two out of the three inflammatory markers (i.e. body temperature, white blood cell count, and C-reactive protein)	Mortality from any cause
	Technical success rate of the initial EUS-guided drainage
	Incidence of a biliary stricture and gastrointestinal obstruction
	Number of interventions
	Total procedure time
	Time requiring endoscopic and/or percutaneous drainage
	Length of hospitalisation
	Length of ICU stay
	Duration of antibiotics administration
	Total costs of interventions and hospitalisation
	Incidence of WON recurrence
	Time from clinical success to WON recurrence
	Incidence of a pancreatic pseudocyst
	Incidence of new-onset diabetes
	Incidence of clinical symptoms associated with pancreatic exocrine insufficiency
	Incidence of pancreatic cancer
	Incidence of sarcopenia
	Changes in the morphology and volume of the pancreas

^a^Patients who do not undergo clinical success within 6 months of the randomisation will be treated as cases with clinical failure

Abbreviations: *ASGE* American Society for Gastrointestinal Endoscopy, *EUS* Endoscopic ultrasound; *ICU*, Intensive care unit, *WON* Walled-off necrosis

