## Assignment of interventions: allocation

### Sequence generation {16a}

Eligible patients with WON will be allocated randomly to either the immediate necrosectomy group (experimental group) or the step-up approach group (control group) based on random sequence generated by the web-based system (University Hospital Medical Information Network Internet Data and Information System for Clinical and Epidemiological Research, cloud version [UMIN INDICE Cloud], https://www.umin.ac.jp/indice/cloud.html). The WONDER-01 trial employs the completely randomised design without blocking or stratification.

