## Data collection and management

### Plans for assessment and collection of outcomes {18a}

Clinical parameters at baseline and outcome variables have been pre-defined. To promote the quality of data on the primary endpoint (i.e. clinical success), the expert panel will review the clinical course and CT images upon request. Data on those variables will be collected from the electronic medical chart at each centre. The schedule of enrolment, randomisation, interventions, and assessments is summarised in Table 3.

**Table 3 Tab3:** Schedule of interventions and assessments in the WONDER-01 trial

	Study period					
	Pre-intervention	Intervention (within 6 months of randomisation)				Post-intervention
	≤ 10 days before randomisation		Within 3 days of randomisation	7 days after intervention	Clinical success	After five years of clinical success
	Screening	Randomisation	Intervention		Assessment	Follow-up
Informed consent	X					
Eligibility screening	X					
Assessment of WON	X					
Assessment of symptoms	X				X	
Body temperature	X			X	X	
Blood test^a^	X			X	X	
Imaging study^b^	X			X^c^	X	
Electrocardiogram	X					
Randomisation		X				
Interventions			X			
Assessment of primary endpoint					X	
Assessment of secondary endpoints				X	X	X
Monitoring of adverse events				X	X	X

^a^A blood test includes the following items: white blood cell count, haemoglobin, platelet count, albumin, aspartate aminotransferase, alanine aminotransferase, gamma-glutamyl transpeptidase, alkaline phosphatase, total bilirubin, amylase, lipase, blood urea nitrogen, creatinine, C-reactive protein, and international normalised ratio of prothrombin time

^b^Contrast-enhanced computed tomography is performed unless there are contraindications for contrast use. Magnetic resonance imaging may be performed on the investigator’s discretion

^c^Imaging studies are performed at least every 2–3 weeks during the intervention period

Abbreviation: *WON* Walled-off necrosis

The investigators at each centre will collect relevant patient data from the electronic medical chart and input anonymised data to the trial database. The standardised trial database has been constructed using the Microsoft Access software (Microsoft Corp., Tokyo, Japan) and has been distributed to participating centres. The database file will be uploaded to the online storage that can be accessed only by the investigators.

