## Statistical methods

### Statistical methods for primary and secondary outcomes {20a}

In the primary analysis, we will compare times to clinical success between the immediate necrosectomy and step-up approach groups. In our primary hypothesis testing, cumulative survival probabilities of times to clinical success will be estimated using the Kaplan–Meier product-limit method and be compared using the log-rank test. Patients are censored at the time-point of salvage surgery, the last follow-up, 6 months of the randomisation, or death, whichever came first. In the secondary analyses, we will use Student’s *t*-test or Wilcoxon rank-sum test, as appropriate, for continuous variables; the chi-square test or Fisher’s exact test, as appropriate, for categorical variables; and the log-rank test for time-to-event variables.

The two-sided α level of 0.05 was used for statistical significance for all analyses. All analyses will be conducted for the intention-to-treat population, and examinations of per-protocol population will represent secondary analyses.

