### Methods for additional analyses (e.g. subgroup analyses) {20b}

In subgroup analyses of time to clinical success stratified by clinically relevant parameters (e.g. the size of WON, the proportion of necrotic components in the WON cavity [estimated and classified as < 30%, 30–60%, or > 60% [34], based on preprocedural CT findings], extension status of WON), we will assess statistical heterogeneity in the hazards by a specific variable by evaluating the Wald test on a cross-product of the variable and the treatment group in the Cox proportional hazards regression model. The multivariable Cox regression model will be used to adjust for potential imbalance of confounders and to calculate hazard ratios for clinical success comparing the immediate necrosectomy to the step-up approach.

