### Methods in analysis to handle protocol non-adherence and any statistical methods to handle missing data {20c}

In the primary analyses of time to clinical success, patients who lose to follow-up will be treated as censored cases at the time of the last follow-up. In multivariable Cox regression models, we will assign a major category for missing data on categorical covariates and a mean or median value, as appropriate, for missing data on continuous covariates. We will confirm that excluding cases with missing data does not alter our findings substantially. In the analyses of the secondary endpoints, patients with missing data on the corresponding variable will be excluded.

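### Change in pancreatic volume falls under an unadjusted two-sample test although a screening scan is scheduled, so the comparison is valid but less precise than a baseline-adjusted one

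*Protocol article*

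**What the plan says.** - **Endpoint.** Table 1 (Objectives {7}) ends its list of secondary endpoints with "Changes in the morphology and volume of the pancreas". It is the only secondary endpoint worded as a change.
- **Test.** Statistical methods for primary and secondary outcomes {20a} assigns continuous secondary variables to Student's t-test or "Wilcoxon rank-sum test, as appropriate, for continuous variables". Neither test has a covariate. Pancreatic volume is not named there and comes under the rule as a continuous variable. The same section states: "The two-sided α level of 0.05 was used for statistical significance for all analyses".
- **Baseline scan.** Table 3 (Plans for assessment and collection of outcomes {18a}) marks imaging at screening, during the intervention period and at clinical success. Its footnote says "Contrast-enhanced computed tomography is performed unless there are contraindications for contrast use", and it leaves MRI to the investigator's discretion.
- **Randomisation.** Sequence generation {16a}: "The WONDER-01 trial employs the completely randomised design without blocking or stratification".
- **Covariate adjustment elsewhere.** The only adjusted model is in Methods for additional analyses {20b}: "The multivariable Cox regression model will be used to adjust for potential imbalance of confounders and to calculate hazard ratios for clinical success". It serves time to clinical success alone.
- **Missing data.** For secondary endpoints, section {20c} says that "patients with missing data on the corresponding variable will be excluded".

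**The concern.** A two-sample test on the change uses the baseline scan by subtraction, which fixes the coefficient of baseline at 1. ANCOVA estimates that coefficient. When follow-up is imperfectly correlated with baseline, subtracting the whole baseline value adds noise and over-corrects for any baseline difference between the arms.

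Two things are at stake, both confined to this endpoint: a wider confidence interval than the same scans could give, and an estimate that moves with whatever baseline difference the randomisation happens to produce. Nothing in the design limits that difference. For the primary endpoint the authors do provide for adjustment for imbalance, but they make no such provision for the one secondary endpoint whose own baseline value is scheduled to be imaged.

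This concerns a stated method and is not a complaint that detail is missing. The article names the tests for continuous secondary variables.

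**Working it through.** **The plan's own figure.** The article gives no calculation for pancreatic volume. Its only sample size, 64 before dropout, is for the log-rank test on the primary endpoint. It reproduces: with exponential times, HR = ln(0.40)/ln(0.65) = 2.127, 36 months of accrual, 6 months of follow-up, two-sided 0.05 and power 0.80, the Lachin–Foulkes formula gives 63.4, rounded up to 64. The present point does not touch it.

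**Inputs.** From the article: N = 70, 35 per arm, two-sided 0.05. Assumed: a correlation r between baseline and follow-up volume of 0.3 to 0.9, and the same SD (set to 1) at both scans.

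**Step 1: variance.** Per patient:
- change score: 2(1 − r)
- ANCOVA: 1 − r²
- ratio, change to ANCOVA: 2(1 − r)/(1 − r²) = 2/(1 + r)

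The SE of the arm difference is the square root of the variance times 4/70. The information equivalent is the N at which ANCOVA would match a change-score analysis of 70, that is 70(1 + r)/2.

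| r | Variance ratio | SE, change | SE, ANCOVA | ANCOVA N matching 70 |
|---|---|---|---|---|
| 0.3 | 1.54 | 0.283 | 0.228 | 45.5 |
| 0.5 | 1.33 | 0.239 | 0.207 | 52.5 |
| 0.7 | 1.18 | 0.185 | 0.171 | 59.5 |
| 0.8 | 1.11 | 0.151 | 0.143 | 63 |
| 0.9 | 1.05 | 0.107 | 0.104 | 66.5 |

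ANCOVA pays for one more parameter, a factor of about 1 + 1/(70 − 4) = 1.015. The ratios then become about 1.52, 1.31, 1.16, 1.09 and 1.04.

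The direction does not depend on equal SDs. With SDs s0 at baseline and s1 at follow-up, the change-score variance minus the ANCOVA variance is s0² + s1² − 2r·s0·s1 − s1²(1 − r²) = (s0 − r·s1)², which is never negative.

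**Step 2: power.** For a true difference of 0.5 SD (assumed), normal approximation, 35 per arm:

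| r | Change score | ANCOVA |
|---|---|---|
| 0.3 | 42% | 59% |
| 0.5 | 55% | 68% |
| 0.7 | 77% | 83% |
| 0.8 | 91% | 94% |
| 0.9 | 99.7% | 99.8% |

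**Step 3: chance imbalance.** The baseline difference d between the arms has SE √(4/70) = 0.239 SD. The probability that it exceeds 0.3 SD in either direction is 2[1 − Φ(0.3/0.239)] = 21%. Given d, the change-score contrast shifts by (r − 1)d. For d = 0.3 SD that is −0.15 SD at r = 0.5, −0.09 at 0.7 and −0.03 at 0.9. The conditional type I error of the change-score test is then 6.3%, 5.9% and 5.3%. With d = 0 it is 2.4%, 3.4% and 4.4%. Averaged over d it is the nominal 5%.

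**Step 4: Student's or Welch's test.** Simple randomisation gives exactly 35/35 with probability 9.5%, and a split of 30/40 or more uneven with probability 28%. I simulated normal data with an SD ratio of 2 (assumed). With the larger SD in the smaller arm, Student's type I error is about 7.4% at 30/40 and 8.4% at 28/42. In the reverse case it is 3.4% and 2.8%. Averaged over the actual distribution of arm sizes it is about 5.3%. Welch's test stays at about 5% throughout.

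**The case against.** **It is analysis-plan detail.** The rule in {20a} is one generic sentence that does not name pancreatic volume, and this is the last of 19 secondary endpoints, partly descriptive. A two-sample test of change is valid, and nothing is contradicted. That stands as a limit on importance. It does not remove the point, because the article does state a method for continuous variables and a better use of the same data costs nothing.

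**The change-score result is biased.** A reader might infer this from the unrestricted randomisation. The article does not support it: over randomisations the contrast is unbiased and keeps its type I error. Only the conditional shift in Step 3 remains.

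**The loss may be negligible.** The same organ is scanned twice in the same patient, so a high correlation cannot be excluded, and at r = 0.9 the penalty is 5%. This stands, and it is why the whole range is shown.

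**Thirty-five per arm is not assured.** The article does not say which scan defines the change. Patients without clinical success have no visit of that name, although imaging continues every 2–3 weeks during the intervention period. If the scan at clinical success is used, it may fall at different times in the two arms, which baseline adjustment does not cure. Nor does the schedule prove that every patient has a usable baseline volume: contrast may be omitted, MRI is allowed, and missing values are excluded. All of this stands. It lowers the power figures for both analyses but leaves the variance ratios unchanged, because they do not depend on n.

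**Student's test is unsafe here.** A reader might infer this from the conditional figures of 7.4% and 8.4%. They need an SD ratio of 2, for which the article gives no support, together with an uneven split in the unfavourable direction. The unconditional rate is close to nominal, and the rank-sum test is also allowed.

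**Conclusion.** The point holds as a small, free improvement. The stated rule gives a valid comparison of change in pancreatic volume that is less precise than one adjusted for baseline. The variance penalty runs from 54% at r = 0.3 to 5% at r = 0.9, before the 1.5% cost of the extra parameter. This rests on an assumed correlation, on equal SDs for the exact ratios, and on the t-test form of the analysis; no figure was derived for the rank-sum test. The exposure to chance imbalance is conditional only, at most a few hundredths of an SD at high correlation and 0.15 SD for a 0.3 SD imbalance at r = 0.5. The gain from Welch's test is minor. The primary log-rank analysis, the 64 and 70 patients, and the trial's main conclusion are untouched.

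**What to change.** Before the analysts see results by arm, state that follow-up pancreatic volume is analysed by ANCOVA with baseline volume as covariate, on the log scale or by a rank-based version if the distribution is skewed. Report the adjusted difference (or ratio) with a 95% CI. The same wording should name the scan that counts as follow-up, since the model needs it.

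Optionally, use Welch's test wherever Student's test would be chosen for other continuous endpoints. It guards against unequal variances in arms of unequal size at almost no loss.

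The cost is a few lines of text. No additional scan, visit or patient is needed.

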### Trial design {8}

The WONDER-01 trial is designed as a multicentre, open-label, parallel-group, randomised controlled trial that evaluates the superiority of immediate DEN over drainage-oriented step-up approach in terms of time to clinical success among patients receiving EUS-guided drainage of WON. Patients diagnosed with symptomatic WON will be screened for the inclusion and exclusion criteria. Eligible patients will be randomised at a 1:1 ratio to either the immediate DEN group or the step-up approach group.

The WONDER-01 trial has been designed and will be implemented by the WONDERFUL (WON anD pERipancreatic FlUid coLlection) study group, which consisted of expert endoscopists, gastroenterologists, interventional radiologists, and epidemiologists at high-volume centres in Japan [27, 28].

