### Sample size {14}

For the sample size calculation, we assumed that the rates of clinical success at 60 days of the initial EUS-guided drainage were 60% in the immediate necrosectomy group and 35% in the step-up approach group according to preliminary data from a retrospective analysis by the WONDERFUL study group (under submission). When we planned 36 months for patient accrual and 6 months for follow-up, 64 patients were required with a two-sided α level of 0.05 and a power of 0.80. Taking the dropout into account, we planned a sample size of 70 patients (35 patients per arm).

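### Student's t-test is paired with unblocked randomisation, so its error rate can drift from 5% if the SDs differ; Welch's version removes this almost free, and Boschloo's test would modestly help where Fisher's would be used

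*Protocol article*

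**What the plan says.** The protocol article, under Statistical methods for primary and secondary outcomes {20a}, offers two tests for each type of secondary endpoint. Continuous variables get Student's t-test or the "Wilcoxon rank-sum test, as appropriate, for continuous variables". Categorical variables get "the chi-square test or Fisher’s exact test, as appropriate, for categorical variables". On the error rate it says: "The two-sided α level of 0.05 was used for statistical significance for all analyses".

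Sequence generation {16a} states: "The WONDER-01 trial employs the completely randomised design without blocking or stratification". Trial design {8} gives the ratio ("Eligible patients will be randomised at a 1:1 ratio"), and Sample size {14} plans 70 patients, 35 per arm.

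The continuous secondary endpoints in Table 1 include procedure time, hospital and ICU stay, antibiotic duration and costs. The categorical ones include some that may be sparse, such as death, biliary stricture and pancreatic cancer. No SDs or event rates are given for any of them.

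**The concern.** Student's t-test pools the two variances. With equal arms this does little harm even when the variances differ. With unequal arms the pooled standard error is too small if the smaller arm is the more variable, and too large if the larger arm is. Randomisation without blocks makes unequal arms likely. The exclusion of patients with missing secondary data (section {20c}) can shift the analysed numbers further.

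Unequal SDs are plausible, because one arm starts necrosectomy at once while the other is observed and escalated on demand. At stake are the p-values for durations and costs, which could be too liberal or too strict depending on a chance split.

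A smaller matter concerns sparse complications. Fisher's test works well below 5% there, so some power to detect a difference in harms is given up.

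**Working it through.** **Inputs.** From the protocol: N = 70, ratio 1:1, no blocking, two-sided 0.05, and the named tests. Assumed: independent 1:1 draws; normal data; SD ratios of 1.5, 2 and 3; Fisher used when an expected count is below 5 and chi-square otherwise (the protocol does not define when each is appropriate).

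**1. The plan's own figure.** For these tests it is the nominal 5%. With equal SDs, simulation (200,000 runs per split) gives Student's t 5.0 to 5.1% at 35/35, 30/40 and 27/43. The nominal level is reproduced.

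**2. How unequal the arms get.** With n1 ~ Bin(70, 0.5):
- P(30/40 or worse) = 2 × P(n1 ≤ 30) = 0.282
- P(exactly 35/35) = 0.095
- central 95% range: 27/43 to 43/27

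**3. Why Student's t drifts.** Take SDs of 2 and 1 at 30/40.
- Larger SD in the arm of 30. True variance of the difference: 4/30 + 1/40 = 0.158. Expected pooled estimate: [(29 × 4 + 39 × 1)/68] × (1/30 + 1/40) = 2.279 × 0.0583 = 0.133. Ratio of standard errors: √(0.133/0.158) ≈ 0.92, so too small.
- Larger SD in the arm of 40. True: 4/40 + 1/30 = 0.133. Pooled: [(39 × 4 + 29 × 1)/68] × 0.0583 = 0.159. Ratio: √(0.159/0.133) ≈ 1.09, so too large.

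**4. Simulated true level of Student's t.**

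| Arm with the larger SD | SD ratio 1.5 | SD ratio 2 | SD ratio 3 |
|---|---|---|---|
| 35 of 70 | 5.1% | 5.2% | 5.2% |
| 30 of 70 | 6.4% | 7.4% | 8.4% |
| 27 of 70 | 7.3% | 9.0% | 10.7% |
| 40 of 70 | 3.9% | 3.4% | 3.0% |
| 43 of 70 | 3.3% | 2.5% | 2.0% |
| Averaged over all splits | 5.1% | 5.3% | 5.6% |

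Welch's test is between 4.95% and 5.07% at every split and ratio tried. Power with equal SDs and a standardised difference of 0.68, Student / Welch: 80.0 / 80.0% at 35/35 and 77.8 / 77.5% at 27/43.

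**5. Categorical endpoints (exact enumeration of all 2×2 tables).**
- Fisher's maximum true level: 2.9% at 35/35, 3.9% at 30/40. At 35/35 it is 1.3% when 10% have the event and 0.3% when 5% do.
- Boschloo's maximum: 4.8% at 35/35, 4.7% at 30/40. At 35/35 it is 2.7% and 1.1% at those two event rates.
- The chi-square-or-Fisher rule: maximum 5.2% at 35/35, 5.3% at 30/40.

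Power at 35/35:

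| True rates | Chi-square-or-Fisher rule | Boschloo throughout |
|---|---|---|
| 3% v 15% | 23% | 33% |
| 2% v 12% | 14% | 25% |
| 5% v 20% | 38% | 41% |
| 10% v 30% | 55.4% | 54.2% |
| 20% v 50% | 77.2% | 75.7% |

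In the limiting case of 0% v 12% the figures are 24% and 41%. As an illustration, 0 v 5 events at 35/35 gives Fisher p = 0.054, and Boschloo rejects.

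At 30/40 and 3% v 15%, Boschloo and Fisher have the same power (28.3% with the lower rate in the arm of 30, 34.6% with it in the arm of 40). At 10% v 30%, with the lower rate in the arm of 30, Boschloo throughout has 49.1% against 55.0% for the rule.

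Using Boschloo's cut-off only where the rule would call for Fisher, and chi-square elsewhere, leaves the maximum level at 5.2% (35/35) and 5.3% (30/40), the same as the rule now.

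**The case against.** The strongest reply is that nothing in section {20a} is wrong. The tests are conventional, the endpoints are secondary, Wilcoxon and chi-square stand in the same sentences, and an analysis plan not shown may say when each applies. Much of this stands. Outcomes such as length of stay may well go to Wilcoxon, and then the Student's t problem does not arise. The 7.4% needs a t-test, unequal SDs, and an unequal split with the more variable arm smaller. At a fixed SD ratio, a split of 30/40 or worse in that direction has a probability of half of 28%, about 14%. The reply does not dispose of the point, because the protocol itself names Student's version, and the trial is analysed at the one split that it gets, not at the average.

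Three stronger readings are tempting and are not supported:
- *Fisher's test fails its 5% level.* It does not: its error stays below 5% at every split and rate examined. It is conservative.
- *Lack of blocking alone breaks Student's t.* With equal SDs it is at its nominal level at any split, and averaged over splits it is at most 5.6% even at an SD ratio of 3.
- *Boschloo beats the written plan at no cost.* Against Fisher alone, 10% v 30% at 35/35 looks like a gain from 46% to 54%. At those rates the plan would usually use chi-square, and the comparison becomes 55.4% v 54.2%, a small loss.

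**Conclusion.** The point holds as a minor improvement. If a t-test is used for a continuous secondary endpoint and the SDs differ twofold, Student's true level at 30/40 is about 7.4% or 3.4%, depending on which arm is the more variable, against about 5% for Welch's. This rests on an assumed SD ratio, on normal data, and on reading the randomisation as independent draws. If the arms were in fact held at 35/35, Student's would be within about 0.2 points of nominal.

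The point on Fisher's test is weaker. It concerns lost power, not lost error control, and it matters only in sparse tables at or near equal arms. Neither point touches the primary analysis or the sample size.

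**What to change.** Replace Student's t-test with Welch's t-test in section {20a} and keep Wilcoxon as the alternative. This changes one name and uses standard software. With equal SDs the cost is at most about 0.3 points of power. With unequal SDs, Welch's has less power than Student's when the smaller arm is the more variable (73% v 82% at 27/43 in one simulated case with an SD ratio of 2), but Student's advantage there comes with its inflated level. In the reverse case Welch's has more (85% v 77%).

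Optionally, where expected counts would lead to Fisher's test, use Boschloo's exact test instead and keep chi-square for the other tables. The cost is a less familiar test to explain. The gain is confined to rare events at or near equal arms and should be described in those terms.
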